**Longitudinal Component objective**

To create and develop new and improved risk stratifications models for men diagnosed with prostate cancer. By risk we mean the probability of developing cancer, cancer progression, metastasis and death.

We aim to explore this risk in relation to characteristics measured in men at baseline. These characteristics will be collected from clinical records, mpMRI images, blood, urine and biopsy tissue samples.

## Primary Outcome

### **Cross sectional component primary outcome**

Presence of clinically significant prostate cancer confirmed on biopsy, defined as any Gleason pattern 7 or greater.

### Longitudinal Component primary outcome

Time to metastasis and/or prostate cancer related death.

## Secondary Outcomes

- Time to new prostate cancer in men without cancer at baseline
- Time to cancer progression* in men identified with prostate cancer at baseline
- Time to prostate cancer specific death and all-cause death in all men.

** Need for salvage therapy to the prostate following the primary treatment strategy, or, need for systemic therapy for prostate cancer treatment following failure of the primary treatment strategy.*

# STUDY DESIGN

ReIMAGINE Prostate Cancer Risk is a multi-centre, prospective, observational, longitudinal cohort study of men referred to secondary care with a suspicion of prostate cancer or men who are undergoing further tests for prostate cancer staging assessment. Men with a serum PSA level of 20ng/ml or less, whose mpMRI scan has been scored as PIRADS/LIKERT score 3, 4 or 5, and who have been advised and accepted the need for a targeted and systematic prostate biopsy will be invited to enrol.

Men will be recruited across a number of high-volume NHS centres which already have an mpMRI based diagnostic pathway. The study has an initial cross-sectional component where consenting men will be asked to donate blood, urine, imaging files and prostate biopsy tissue for biomarker analysis before or at the time of their standard of care prostate biopsy.

After collection of the cross-sectional biological samples within ReIMAGINE, men will revert to NHS standard of care, attending a routine outpatient appointment for the results of their prostate biopsy outside of the trial setting. Although there are no further planned study visits all men will be consented for healthcare data linkage to measure long-term outcomes including cancer progression, development of metastases and mortality for the longitudinal component of the study.

The ReIMAGINE team aim to recruit 1,000 men with a PIRADs/LIKERT score 3, 4 or 5 who are undergoing an MRI-directed prostate biopsy. Of these 1,000 biopsies, we anticipate that 60% will have any cancer detected on histology (3+3 or greater) giving approximately 400 cases of clinically significant cancer (Gleason 7 or more).

After 12 months of accrual to the study an interim review will be performed by the ReIMAGINE scientific advisory board *(see appendix I for SAB membership)* who will review both accrual rates and cancer incidence with the remit of reviewing and advising on the final recruitment target.

# STUDY SCHEDULE

## Screening and Registration

Potential participants will be identified in a routine secondary care setting of the participating NHS sites by their clinical care team or ReIMAGINE funded staff. Participants may be identified at the point of referral to the hospital, within urology cancer clinics or by other means such as waiting lists or review of case records of the same NHS sites.

First approach of potential participants will predominantly occur via telephone and/or invitation letter conducted or sent by a ReIMAGINE staff member (clinical trials practitioner) following receipt and review of a primary care referral to the recruiting site. As some recruiting sites run a “one-stop” prostate cancer clinic, whereby men are biopsied on the same day as their MRI, the study protocol will include the option to send out a PIS to potential participants and call them to explain the study and discuss any questions they may have, following the clinical team having already explained the clinical standard pathway. As the time window between the MRI (which has to be reported to confirm eligibility) and biopsy (which can only be performed after blood and urine sample collection) is minimal approach by telephone is key to accrual.

If approached via telephone potential participants will be asked for their willingness to receive a patient information sheet (post/email) which will be sent in advance of their clinical appointment. All participants considered for recruitment onto the ReIMAGINE study will be recorded on the study participant screening log. To ensure completeness of data, any patient who receives a patient information sheet for the ReIMAGINE study- either at a face to face consultation, or through the postal service or email- will be included on the study participant screening log.

Consent will also be discussed over the phone and affirmation will be noted both on the eCRF and in medical records (electronic or paper), and on the day that the participant attends clinic for the first visit, wet signature will be obtained, to substantiate affirmation.

Recruiting sites will register fully eligible and consenting patients using a software system (Research Data Collection Service - REDCap) hosted securely by UCL and Phillips (pseudonymised data only). After providing full informed consent, each patient will receive a unique patient ID. An additional separate REDCap database will be hosted securely by University College London (only) to handle identifiable data used for healthcare data linkage purposes.

Following consent, participants will be registered and screened against inclusion/exclusion criteria to confirm eligibility prior to registration (see section 7). Any participant who meets all the inclusion criteria and none of the exclusion criteria will be offered to continue with the study and will be registered. They will attend a baseline visit in order to start collecting baseline measurements.

Eligible men will be invited to consent to the following:

- Agreement to have blood and urine taken for biomarker assessment.
- Agreement for up to 3 additional prostate biopsy cores to be taken at the time of their standard of care diagnostic prostate biopsy.
- Agreement to share standard of care paraffin processed tumour blocks and H&E slides for additional research analysis. These will be returned to NHS sites.
- Donation of anonymised imaging files / data from their baseline MRI scan.
- Agreement to healthcare data linkage through NHS Digital, Public Health England and/or other relevant bodies.

Any patient who provides full informed consent to the study but does not fulfil all other eligibility criteria will be recorded as a screen failure. These screen failure patients will not receive a unique patient ID number.

**Visit 1**

Where participants are found to be eligible the following baseline information and assessments will be recorded prior to registration:

***Demographic and general measurements***

- Medical history
- Demographics
- Family History
- Ethnicity
- Age
- Co-Morbidities
- Medication use

All consented patients who are deemed eligible will have already been advised and/or have a scheduled visit for a prostate biopsy on clinical grounds as standard care. On the day of consent or at the time of the scheduled prostate biopsy participants will have the below interventions:

- Donation of blood will be drawn from men, either via a trained phlebotomist or from the cannula already in situ in preparation for their prostate biopsy.
- Donation of urine. Provided by participant in advance of prostate biopsy.
- Up to three additional biopsy cores will be taken at the time of the standard of care biopsy. Two cores will be taken from the radiologically guided area of suspicion and one control sample from the contralateral non-suspicious area.

**Non-Visit**

After the standard of care prostate biopsy is reported, and in line with participant consent, delegated ReIMAGINE staff members, will request access to the formalin fixed paraffin embedded (FFPE) tissue blocks and H&E (Haematoxylin and Eosin) stained slides from this prostate biopsy.

H & E slides will be anonymised, scanned using high resolution scanners, uploaded to the ReIMAGINE image databank and returned to the NHS pathology department it was requested from.

A tissue technician will acquire slices from the requested FFPE tissue blocks in line with the study SOP and return the block to the hospital pathology department after tissue capture. The acquired slices will be stored in the UCL Cancer Institute laboratory and transported in batches to ReIMAGINE consortium partners.

**Analyses**

Components of blood (white blood cells, plasma, serum) urine and tissue will be subjected to molecular analyses, including genomic, mRNA expression and protein studies by the RE-IMAGINE consortium academic and industry partners. These will include but not be exclusive to next-generation sequencing, whole-genome micro-array expression profiling, immunohistochemistry and immunofluorescence and ELISA tests.

ReIMAGINE Prostate Cancer Risk will be looking to redefine a new clinical metric for significance in relation to prostate cancer (excluding imaging and biomarkers initially).

**Long term healthcare data linkage**

The study will obtain informed consent from participants to collect long term healthcare information from national records, such as the Office for National Statistics, NHS Digital, Public Health England, and/or other applicable NHS information systems, or national databases. No further visits will be required for this activity, but permission will be obtained to receive and hold this information. The research team will collect this healthcare information up to three years after last patient last visit (LPLV) and further funding will be sought to collect this longer term (until death time point should funding be successful).

**Figure 2:** ReIMAGINE Prostate Cancer Risk Trial Flow Diagram

*
[figure not shown]
*

** Blood and Urine collection will always occur before the prostate biopsy is performed but may not always be on the same day as the biopsy procedure.*

**Table 1:** Schedule of Assessments

| **Visit** | **Screening & Registration** | **Visit 1*** | **Non-Visit** | **In direct collection** |
| --- | --- | --- | --- | --- |
| Timing of Visit | Day -1 | Day 1 | 3-6 Weeks | n/a |
| Registration | X |  |  |  |
| Medical History | X |  |  |  |
| Eligibility confirmation | X | X |  |  |
| Informed Consent |  | X |  |  |
| PSA | X |  |  |  |
| Research Blood |  | X |  |  |
| Research urine |  | X |  |  |
| Targeted biopsy |  | X |  |  |
| Biopsy results |  |  | X |  |
| FFPE tissue block and H&E slide collection |  |  | X |  |
| Adverse Events review |  | X |  |  |
| Concomitant Medication review (if applicable) | X |  |  |  |
| Healthcare data linkage |  |  |  | X |

** Blood and Urine collection will always occur before the prostate biopsy is performed but may not always be on the same day as the biopsy procedure.*

## Discontinuation/withdrawal of participants

In providing full informed consent to participate in the study, participants are consenting to data collection, screening assessments, sample donation, follow-up and healthcare data linkage.

Sites will be required to complete a protocol deviation form if participants are unable to provide:

- < 10ml of blood. (1x 10ml EDTA tube)
- < 10ml urine
- < 1 prostate tissue core

A participant may be withdrawn from the study whenever continued participation is no longer in the participant’s best interests, but the reasons for doing so must be recorded. Reasons for discontinuing the study may include:

- - intercurrent illness
  - patients withdrawing consent
  - Persistent non-compliance to protocol requirements.

The decision to withdraw a participant from the study will be recorded in the eCRF and medical notes. If a participant explicitly states that they do not wish to contribute further data to the study their decision must be respected and recorded in the eCRF and medical notes. Should any participant withdraw from the study, any information that has already been obtained will be kept, in line with the Data Protection Act (2018) and General Data Protection Regulations (GDPR).

## Definition of End of Study

**For each man**

Following consent and sample collection (blood, urine, prostate tissue), men will revert back to the NHS standard of care pathway. Men will be booked into a routine NHS clinical appointment to receive the result of their standard of care prostate biopsy. Men will undergo follow-up for 4-8 weeks to gather information from their medical records (i.e. the result of the biopsy) at which time active data collection for the cross-sectional component will end. Men will then transition to the longitudinal component of the study and will be followed up via data linkage (initial 3-year period).

For the cross-sectional component, end of study is defined as database lock.

For the longitudinal component end of study is defined as database lock.

# CONSENT

Before any study-related procedures are performed (blood, urine or tissue capture), the Principal Investigator or his/her delegate will obtain full written informed consent from a participant. Participants can withdraw consent and decide not to remain in the study at any time without their care being affected.

Participants considered potentially eligible will be approached by a member of the ReIMAGINE team (clinical trials practitioner) or routine clinical team. There are several approach points when this may occur, all of which must be before the prostate biopsy is performed:

- Via telephone upon receipt of a primary care referral to the recruiting centre.
- In clinic before the MRI has been performed and/or reported.
- In clinic after the MRI has been reported and the potential participant has been clinically advised to have a prostate biopsy (which may occur later that day).
- Via telephone after the MRI has been reported and the potential participant has been clinically advised to have a prostate biopsy (which has been or is in the process of being scheduled).

Potential participants will be provided with verbal and written details about the study (ReIMAGINE detailed Patient Information Sheet/Informed Consent Form [PIS/ICF]) or sent the relevant material in the post. This will include detailed information about the rationale, design and activities of the study. Participants will also be provided with a contact point (ReIMAGINE dedicated CTP) where he may obtain further information about the study.

[figure not shown]

It is the responsibility of the Principal Investigator (PI), or a person delegated by the Investigator to obtain written informed consent from each participant prior to any study specific procedures, following adequate explanation of the aims, methods, anticipated benefits and potential hazards of the study.

The person taking consent will be suitably trained, qualified, experienced and competent to participate according to the ethically approved protocol, principles of Good Clinical Practice (GCP) and Declaration of Helsinki 1996.

Anyone other than the PI who is taking consent will have been delegated this duty by the PI on the ReIMAGINE study delegation log. Where this task has been delegated to another member of the team, the PI retains overall responsibility for the informed consent of participants.

It must be recorded in the medical notes when the patient information sheet (PIS) has been given to a participant.

Following the provision of study information, participants will have as long as they need to consider participation (within the limitations of study duration) and will be given the opportunity to discuss the study with their family and other healthcare professionals before they are asked whether they would be willing to take part. Where participants wish, and in cases of participants having to travel a long distance to access a study site, they will be able to provide consent during the same visit that the Patient Information Sheet was provided or be given the option to provide telephone consent. Alternatively, they may return for a separate visit to provide consent, if this is suitable for the participant.

The Investigator or designee must explain that participants are under no obligation to enter the study and they are not required to provide a reason. It must be explained that they can withdraw at any time during the study, without having to give a reason and without prejudicing his further treatment.

No study-specific procedures will be conducted prior to the participant providing full informed consent.

A copy of the signed informed consent form will be given to the participant. The original signed form will be retained in the study file at site and a copy placed in the medical notes. The PIS and consent form will be reviewed and updated where necessary throughout the study (e.g. where new safety information becomes available) and participants will be re-consented as appropriate. It is the responsibility of the PI to ensure this is done in a timely manner.

**Loss of capacity following informed consent**

Loss of mental capacity of a participant after giving informed consent for the study is expected to be a rare occurrence. In this case no further study procedures or data collection will occur. Any data collected up to the point of withdrawal will be kept on record and used in the study analysis.

# ELIGIBILITY CRITERIA

## Inclusion Criteria

- Any man with PSA 20 or less *(value recorded <12 months before study entry)*
- Men who have undergone a prostate MRI as a standard NHS diagnostic work-up.
- MRI lesion conforming to Likert/PIRADS 3, 4 or 5
- Radiological stage T3b or less
- Clinical or radiological stage N0 and M0
- No anti-androgen exposure in the preceding 6 months (5-alpha reductase inhibitors permitted)
- No prior treatment for prostate cancer (chemical, biological, ablative, surgical, radiotherapy)
- Previous TURP is permitted
- Willing and able to provide written informed consent.

## Exclusion Criteria

- Men unable to donate tissue, blood or urine.
- Previous prostate cancer treatment
- Previous prostate biopsy <12 months from date of the mpMRI scan used to assess study eligibility (scoring PIRADs/LIKER 3, 4 or 5).

# RECRUITMENT

All eligible participants referred to secondary care with a suspicion of prostate cancer will be considered for screening. Potential participants will be primarily identified at the point of referral or during routine secondary care urology cancer clinics of the participating NHS sites by their clinical care team or REIMAGINE funded staff. Alternatively, participants may be identified by other means such as waiting lists or review of case records).

All screening and formal eligibility assessments will subsequently take place in the same NHS clinics, dedicated research clinics or on the surgery ward (in preparation for their biopsy) of the study sites.

Research sites will be required to have obtained local, ethical and management approvals and undertake a site initiation meeting prior to the start of recruitment into the study.

# STATISTICAL METHODS

**Sample Size Calculation**

Men suspected of having prostate cancer will be offered an MRI as part of usual care. Our aim is to recruit men with an MRI lesion scoring 3, 4 or 5 who undergo a biopsy.

The ReIMAGINE team will approach approximately 1,777 men with the study PIS.

Of the 1,777 men approached, 1,333 (75%) based on current literature will be expected to be recorded with PIRADs/LIKERT 3, 4 or 5 and advised to undergo a biopsy. The 444 men with PIRADS/LIKERT 1 or 2 will be excluded from taking part in ReIMAGINE Prostate Cancer Risk.

1,333 men will be offered an MRI-directed biopsy with some additional systematic tissue sampling from the non-MRI-directed areas. We expect 25% will reject biopsy or entry to the study which means 1,000 will have the biopsy procedure after consenting to ReIMAGINE Prostate Cancer Risk.

Of these 1,000 biopsies, we anticipate that 60% will have any cancer detected on histology (Gleason 3+3 or greater) yielding 600 cases of cancer and of these we expect about 396 (66%) will have clinically significant cancer i.e. any Gleason pattern 7 or greater.

Therefore, for the cross-sectional component of the analysis we anticipate 600 cases of cancer and 400 cases of no cancer. We will have 396 cases of clinically significant cancer and 604 cases of no cancer or insignificant cancer.

**Statistical Analysis**

All statistical analyses will be conducted according to pre-specified statistical analysis plans that will be agreed prior to the inspection of any outcome data. Logistic regression modelling will be used to analyse the factors associated with presence of clinically significant cancer. Cox regression modelling (or other appropriate survival methods if there is evidence of non-proportional hazards) will be used to analyse the factors associated with time to new cancers, progressions, metastases and deaths. Initially a list of pre-specified factors will be agreed and these will be analysed in the models using a stepwise approach to identify those that are independently associated with the outcome.

In addition to the simple frequentist analysis approach, a more sophisticated analysis will be conducted. We will first apply the SaddlePoint Signature multivariate Bayesian regression pipeline, which was designed specifically for regression with high-dimensional covariates, in order to generate (i) optimal predictive covariate selections (suppressing false positive associations), (ii) quantitative characteristics of true associations (including covariate interactions, if relevant), (iii) personalised multivariate risk signatures, and (iv) quantifiers of the degree of outcome predictability. This will be done both for the full covariate set and for the individual covariate streams (e.g. imaging, genomic, phenotypic), allowing us to compare the outcome prediction power of different information sources, and their potential synergy. The most recent version of the pipeline (version 2.8.6), uses advanced overfitting correction protocols (based on the replica method) and robust internal validation processes. The risk scores for the separate streams will provide intuitive visualisations of the heterogeneity of the patient cohort. In a second stage we will apply Bayesian multivariate latent class analysis, using the source-specific risk signatures computed in the first stage as meta-covariates, and assess whether and how the cohort should be further stratified into subgroups with distinct associations and/or base hazard rates.

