# OBJECTIVES

**Cross Sectional Component objective**

To develop a robust baseline risk stratification system for men who are referred with a suspicion of prostate cancer. By risk we mean the probability of harbouring clinically significant prostate cancer.

We aim to explore this risk in relation to characteristics measured in men at baseline. These characteristics will be collected from clinical records, mpMRI images, blood, urine and biopsy tissue samples.

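### Stepwise selection overstates the weak factors it retains, and the latent class stage has no stated protection if it receives in-sample risk signatures

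*Protocol*

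**What the plan says.** Section 9 (Statistical Methods), under Statistical Analysis, describes two analyses that run side by side.

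- **Frequentist models.** Logistic regression for clinically significant cancer, and Cox regression for new cancer, progression, metastasis and death. A list of factors is agreed in advance, and these are "analysed in the models using a stepwise approach to identify those that are independently associated with the outcome". The list length and the entry or removal criterion are not given. No shrinkage or validation is stated for these models.
- **Bayesian pipeline.** This is in addition to the frequentist models and does not build on them. Stage one is a high-dimensional regression that selects covariates and produces risk signatures, for the full covariate set and for each data stream. The protocol states that it uses overfitting correction and internal validation. Stage two is a latent class analysis "using the source-specific risk signatures computed in the first stage as meta-covariates", to see whether the cohort should be divided further.

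The section refers to analysis plans to be agreed before outcome data are inspected. These are not at hand.

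**The concern.** The cross-sectional objective is "To develop a robust baseline risk stratification system for men who are referred with a suspicion of prostate cancer". That requires effect estimates and risk separation that hold up in new men.

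A stepwise procedure keeps a factor when its estimate in this sample happens to be large enough. The estimate then reported has already passed that filter, so weak factors look stronger than they are, and the usual p-values and intervals take no account of the filter. Agreeing the list beforehand limits the search but does not remove selection within the list.

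In the Bayesian arm, a signature fitted to a man's own outcome carries some of that outcome's noise. If the same fitted values are then covariates for the same outcome in the latent class stage, the noise can appear as separation between subgroups. The safeguards described belong to stage one. The text does not say whether the signatures passed on are out-of-sample, and it states no validation of stage two. At stake are the factors named as independent and any subgroup split that is reported.

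**Working it through.** **1. The plan's own figures (Sample Size Calculation).**

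- "The ReIMAGINE team will approach approximately 1,777 men with the study PIS"
- "Of the 1,777 men approached, 1,333 (75%) based on current literature": 1,777 × 0.75 = 1,332.75, so 1,333.
- "We expect 25% will reject biopsy or entry to the study which means 1,000 will have the biopsy procedure": 1,333 × 0.75 = 999.75, so 1,000.
- "Of these 1,000 biopsies, we anticipate that 60% will have any cancer detected on histology": 1,000 × 0.60 = 600.
- "of these we expect about 396 (66%) will have clinically significant cancer": 600 × 0.66 = 396, leaving 1,000 − 396 = 604.

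All reproduce. The logistic model therefore has n = 1,000 and an event proportion of 0.396.

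**2. Overstatement of a retained weak factor.** Assumptions: a standardised factor independent of the others, true odds ratio 1.15 per SD, retention at two-sided p<0.05. The effect size and the criterion are not in the protocol.

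- True log odds ratio: ln 1.15 = 0.1398.
- Approximate standard error: 1/√(1,000 × 0.396 × 0.604) = 1/√239.2 = 0.0647.
- Expected z: 0.1398/0.0647 = 2.16.
- Chance of retention: Φ(2.16 − 1.96) = Φ(0.20) = 0.58.
- Mean z given retention: 2.16 + φ(0.20)/Φ(0.20) = 2.16 + 0.391/0.580 = 2.84.
- Ratio to truth: 2.84/2.16 = 1.31, an overstatement of 31%. The reported odds ratio averages exp(2.84 × 0.0647) = 1.20.

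Simulation supports this. Backward selection on 20 candidates, five of them with true odds ratio 1.15, gave a mean retained odds ratio of 1.207 over 200 runs: ln 1.207/ln 1.15 = 0.188/0.140 = 1.34. Further runs at this sample size gave 38-44% with stepwise selection, against 3-7% when the full pre-specified model was kept. Hence the range of roughly 30-45%.

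Sensitivity to the criterion, at p<0.157 (critical z 1.415): 2.16 + φ(0.75)/Φ(0.75) = 2.16 + 0.302/0.772 = 2.55, and 2.55/2.16 = 1.18. A looser criterion reduces the overstatement to about 18%.

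**3. False factors.** With k independent null candidates each tested at 0.05, the chance of at least one false factor is 1 − 0.95^k.

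| k | Formula | Backward selection, simulated |
|---|---|---|
| 10 | 40% | 42% |
| 20 | 64% | 66% |
| 30 | 79% | 78% |
| 50 | 92% | 86% |

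This is ordinary multiplicity. In a direct comparison under two settings, the full model without selection gave 0.38 and 1.73 false factors on average, and stepwise gave 0.39 and 1.65. Stepwise selection does not add to the count, and dropping it does not reduce the count unless multiplicity is also controlled.

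**4. Signatures reused in the same men.** The named pipeline could not be run, so these figures come from stand-ins at n = 1,000 with about 40% events and pure noise. No latent class model was fitted.

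| Stand-in for stage one | In-sample AUC | 10-fold cross-fitted AUC |
|---|---|---|
| Ridge, three streams summed, 10 / 50 / 200 covariates per stream, no covariate selection | 0.60 / 0.71 / 0.89 | 0.48-0.49 |
| Cross-validated lasso, 100 / 200 / 500 covariates | 0.54 / 0.54 / 0.57 | not computed |

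In-sample optimism runs from slight to very large, depending on how the signature is selected and shrunk. Cross-fitting removed it where it was tried.

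**The case against.** **The cross-sectional model is well supplied with events.** This stands as a limit. With 396 events and ten factors there are about 40 events per factor. A factor with odds ratio 1.5 per SD has an expected z of ln 1.5/0.0647 = 6.3 and would almost never be dropped or distorted. The bias concerns weak factors and moves an odds ratio from 1.15 to about 1.20. Coverage of the interval for such a factor, given retention, is also near nominal: (0.580 − 0.025)/0.580 = 0.96. A retained null factor, by contrast, has an interval that excludes 1 by construction.

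**The analysis plan may settle it.** It may set the criterion and the list length. But the protocol itself fixes stepwise selection, and a plan without it would depart from the protocol. For the signatures passed to stage two the objection has more force, since the plan could specify out-of-fold scores.

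**Stronger readings that the document does not support.**

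- A reader might infer that the stepwise models feed the latent class stage. They do not: its inputs are the Bayesian pipeline's signatures.
- A reader might infer that data streams with more variables would win the comparison. Streams are compared in stage one, where overfitting correction and internal validation are stated.
- A reader might infer that inflated subgroups are certain. Stage one is said to suppress false positive associations, and the largest figures above come from a stand-in that keeps every covariate.
- A reader might blame the false-factor count on stepwise selection. The comparison above shows that it is shared by any unadjusted testing.

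**Conclusion.** The point holds in two parts of unequal strength.

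**Stepwise selection: firm, of moderate size.** The protocol chooses a method whose estimates for retained weak factors are biased away from zero, by roughly 30-45% on the log scale for a true odds ratio of 1.15 at p<0.05, and whose p-values and intervals ignore the selection. The size rests on assumed values for the effect and the criterion; at p<0.157 it is nearer 18%. The Cox models use the same approach. The protocol gives no expected event count for them, so no size can be stated; fewer events would mean larger standard errors and more overstatement for the same true effect.

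**Latent class stage: conditional.** If in-sample signatures are passed on, subgroup separation may be inflated, by an amount that depends on the pipeline's own selection and shrinkage. If out-of-fold signatures are used, that source of optimism is removed. The protocol does not say which.

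Both should be changed before the analysis plans are agreed. Neither affects recruitment or data collection.

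**What to change.** **Frequentist models.** Replace stepwise selection with one model per outcome containing the full pre-specified list. Report every factor, whatever its p-value. Penalise the fit if the list is long relative to the events, judging this separately for each Cox outcome. If factors are to be declared independent, name a multiplicity procedure and base the declaration on tests from the full model, because penalised estimates do not come with ordinary p-values. Give bootstrap optimism-corrected AUC (or the survival equivalent) and calibration slope, with all model building repeated in each bootstrap sample.

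**Latent class stage.** State that the signatures entering stage two are out-of-fold (cross-fitted), and that both stages are repeated together inside the resampling loop, so that the reported subgroup separation is validated as a whole.

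**Cost.** Wording in the protocol and analysis plan, and computing time. No extra men, samples or data are needed. Headline AUCs are likely to be somewhat lower and fewer factors will be called independent.
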